##### Phase two - Designing and production of health educational materials:

The designing and production of educational materials will be done with the community participation. A video program, brochures, posters, and overhead transparencies will be in accordance with the local understanding. The general theme of the education will be to address the community on the life cycle of *T. solium*, transmission factors, impacts, and preventive and control measures. Emphasis will be put on constructing good latrines using locally available resources, hygienic use of latrines, washing hands before and after meal, building pig houses using locally available materials and feeding pigs indoor using locally available food stuffs. Other useful messages suggested by the community will be included.

Phase three - Dissemination and evaluation of health educational materials:

##### This will be a controlled randomised intervention trial with pre- and post-intervention examination of the study population. The pre-intervention study will be concerned with assessing the prevalence of porcine cysticercosis and its economic impact to the farmer. The study will also assess human perceptions and practices related to the transmission of *T. solium* infections in the area. Following the pre-intervention study, an intervention will be done in which participants in half of the selected villages will receive the health education while half of the villages will act as control. The village will be the unit of intervention allocation. Allocation of the villages to either intervention or control group will be done on a random manner or matched if randomisation will seem to favour communication between groups. Post-intervention study will be conducted to re-assess human perceptions and practices related to the disease, and the prevalence of porcine cysticercosis. The independent variables are therefore the prevalence of porcine cysticercosis, human perceptions and practices related to the disease, while the dependent variable will be the health education.

**Study population**

Sample size calculation:

Although the village will be the unit of intervention allocation, the main analysis will be based on individuals since from previous study there was little variation in the prevalence of porcine cysticercosis in different villages (coefficient of variation was about 0.1). Therefore the sample size has been calculated using the formula,

n = [(z1 + z2)2 2P (1-P)]/(p1 – p2)2.

In the formula, n is number of pigs required in each group, z1 is the z score for the specified confidence level, and z2 is the z score for the specified power. p1 and p2 are the prevalence of the disease in the intervention and control group respectively, and p1 and p2 P is the average of p1 and p2 (Smith and Morrow, 1996).

The sample size is calculated based on the prevalence of porcine cysticercosis as the main outcome measure. The prevalence of porcine cysticercosis in the area was estimated to be 14.64% adjusted for various confounders ([name], 1999). We would like the present study to have 80% power to detect a significant difference with 95% confidence if the intervention will reduce the prevalence of porcine cysticercosis by 30%. The number of villages required in each group is therefore calculated to be:

n = [(1.96 + 0.84) 2 2 x 0.1244 (1-0.1244)]/(0.1464-0.1023)2

= 878.20.

Approximately 900 pigs will be examined in each of the two groups. A total of 1800 pigs will be examined before intervention and 1800 after intervention.

Selection of villages and study participants:

The number of villages to be included in the study will depend on the number of pig farmers available in the villages. This information will be obtained in the pilot study. All pig farmers in the selected villages will be enrolled in the study.

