The epidemiological cycle of *T. solium* occurs mostly in environments with low socio-economic or low hygiene levels, deficient sanitary facilities, or poor pig rearing practices where pigs can gain access to human faeces. Cysticercosis is most common in developing countries of Latin America, Asia, and Africa (Plancarte *et al.,* 1999). However, due to migration of people and tourism, human cysticercosis is now transmitted world-wide and it is considered as an emerging disease in the United States of America (Flisser *et al.,* 1998). Human cysticercosis has been reported in non pork-consuming communities such as the orthodox community in the USA (Schantz *et al.,* 1992). Studies on *T. solium* infections in Tanzania have largely been based on the infections in pigs, however, the possible medical implication of the parasite has been suggested by the presence of hospital records of human epilepsy and taeniosis in the studied areas ([name], 1999; Boa, unpublished report). A study conducted at household level in 21 randomly selected villages in Mbulu district northern Tanzania, established an overall prevalence of 17.4% (range 3.2-46.7%) of porcine cysticercosis in 770 live pigs examined by lingual examination ([name], 1999). This prevalence is higher than those reported by some similar studies in other highly endemic regions of the world. For example in Nigeria 5.5% of 1 300 pigs examined were found to be infected (Onah and Chiejina, 1995) while in Mexico, a prevalence of 4% was reported in 571 live pigs examined (Sarti *et al.,* 1992). Mbulu district was found to have a high potential for the spread of *T. solium* infections due to identified transmission factors. Out of 425 households observed, 21.6% did not have latrines. Of 198 respondents to interviews, 94.4% allowed their pigs to roam for food, and 41% of the respondents lacked knowledge on how a pig could acquire cysticercosis ([name], 1999). Thus, public health education could contribute in reducing the risk of this severe disease. Several studies have found that neither age nor sex of the pig had a significant association with the prevalence of porcine cysticercosis (Sarti *et al.*, 1992; Onah and Chiejina, 1995; Sakai *et al.*, 1998; [name], 1999). Studies in young pigs have indicated that infection rates are significantly higher in dry than in wet season (De-Aluja *et al.*, 1998; [name], in process). In the study in Mbulu, this was linked to the fact that during dry season pigs are let free to look for food in the fields since at this time crops have been harvested. On the other hand during wet season pigs are housed or tethered to restrict them from destroying crops in the fields. Seasonal prevalence of porcine cysticercosis should be considered when targeting and evaluating control measures.

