**Statistical analysis**

Due to the fact that pigs will be clustered in households that are also clustered in villages and climates, a hierarchical logistic regression model will be used to analyse the data in order to take care of different levels of clustering and possible interactions. The effectiveness of intervention in improving human perceptions and practices will be computed by comparing average scores in the two groups adjusted for baseline values. Change in the prevalence of porcine cysticercosis will be computed and adjusted for important confounders such as age, sex of the pig, and other important household characteristics that might affect the prevalence of the disease. Seasonal prevalence of porcine cysticercosis will be taken into considerations when evaluating the intervention.

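### The stated 80% power treats pigs as independent although villages are randomised, relying on a between-village coefficient of variation of 0.1 that the protocol's own prevalence range makes unlikely

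*Protocol*

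**What the plan says.** In the Protocol, Study population (Sample size calculation), the village is the unit of allocation, yet "the main analysis will be based on individuals since from previous study there was little variation in the prevalence of porcine cysticercosis" between villages; the stated support is that the "coefficient of variation was about 0.1". The aim is "80% power to detect a significant difference with 95% confidence" for a 30% relative reduction from 14.64%. The two-proportion formula gives 878.20, rounded to 900 pigs per group. The formula defines n as pigs, but the result is introduced with "The number of villages required in each group is therefore calculated to be".

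Three other places bear on this:
- The Introduction says that a survey of 21 randomly selected Mbulu villages "established an overall prevalence of 17.4% (range 3.2-46.7%) of porcine cysticercosis in 770 live pigs".
- Allocation of villages to intervention groups the villages by baseline prevalence and randomises within groups.
- Statistical analysis says that "a hierarchical logistic regression model will be used to analyse the data in order to take care of different levels of clustering".

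The number of villages is left open until the pilot study.

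**The concern.** When villages are randomised, between-village variation adds to the variance of the treatment comparison, and examining more pigs in the same villages does not remove it. The protocol sets this aside on the strength of one figure, the CV of about 0.1. If the true CV is larger, the trial has less than 80% power, and a null result could be misread as evidence that health education does not work.

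The two statements about the analysis also pull apart. The 80% belongs to an analysis without clustering, while the only model named allows for clustering.

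**Working it through.** **1. The plan's own figure.** (1.96 + 0.84)² × 2 × 0.1244 × 0.8756 / 0.0441² = 1.7079 / 0.001945 = 878.2. It reproduces and contains no design effect. With 900 independent pigs per group, power is 81%.

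**2. Does the range fit a CV of 0.1?** Inputs from the Introduction: 21 villages, 770 pigs (36.7 per village on average), overall 17.4%, extremes 3.2% and 46.7%. Village sizes are not given.

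- *Smallest raw CV, villages weighted equally.* Put the other 19 villages at (21 × 17.4 − 3.2 − 46.7)/19 = 16.6%. The sum of squares is 14.2² + 29.3² + 19 × 0.8² ≈ 1,072, so the SD is √(1,072/20) = 7.3 points and the CV is 7.3/17.4 = 0.42. Sampling noise alone gives √(0.174 × 0.826/36.7)/0.174 = 0.36. A raw CV of 0.1 is therefore ruled out on this weighting, but a CV of 0.1 with noise removed is not ruled out by this step.
- *Chance of a range of 43.5 points or more.* This is a beta-binomial simulation of 40,000 surveys of 21 villages with mean 17.4%. The village sizes are assumptions.

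| Pigs per village | True CV 0.1 | True CV 0.5 |
|---|---|---|
| 37 in every village | 0.02% | 22% |
| 15 to 58 | 0.9% | 30% |
| 5 to 69 | 8% | 39% |

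- *Rough CV from the range.* The expected range of 21 normal values is 3.78 SD, so SD = 43.5/3.78 = 11.5 points. Removing binomial variance at equal village sizes leaves √(11.5² − 17.4 × 82.6/36.7) ≈ 9.7 points, a CV of about 0.55. This rests on two extremes and is only indicative.

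**3. Power with clustering.** Let p1 = 0.1464 and p2 = 0.7 × 0.1464 = 0.1025, with c villages per group and m pigs per village. For an unstratified design,

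SE² = [p1(1−p1)/m + p2(1−p2)/m + CV²(p1² + p2²)]/c,

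with a noncentral t on 2(c−1) degrees of freedom. Assume c = 21 and m = 43 (903 pigs). The binomial part is 0.2170/43 = 0.005046, and p1² + p2² = 0.03194.

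| CV | CV² part | SE | 0.0439/SE | Power |
|---|---|---|---|---|
| 0.1 | 0.000319 | 0.01598 | 2.75 | 76% |
| 0.25 | 0.001996 | 0.01831 | 2.40 | 65% |
| 0.5 | 0.007985 | 0.02491 | 1.76 | 41% |

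With 10 villages of 90, power is 71%, 51% and 25%. With 29 villages of 31, about the most per group that the district's 59 villages allow, it is 78%, 69% and 48%. Pigs clustered in households (1.8 per farmer in the earlier study) would lower these further.

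**4. If the analysis really ignored clustering.** Take the intraclass correlation as CV² × 0.1464/0.8536, the design effect (DE) as 1 + 42 × that correlation, and the type I error as 2[1 − Φ(1.96/√DE)]. For 21 villages of 43, DE is 1.07, 1.45 and 2.80 at CV 0.1, 0.25 and 0.5, giving a type I error of about 6%, 10% and 24%. These figures apply only to an unadjusted pig-level test.

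**The case against.** Several objections have weight.

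- *The 0.1 is reported as a finding of a previous study.* A reader might infer from the range that 0.1 is impossible. The documents do not support that: they give no village sizes, and the chance of such a range at CV 0.1 moves from 0.02% to about 8% as the assumed sizes become more unequal. The Introduction also does not label the range as by village, although that is the natural reading. The 0.1 might be an adjusted quantity, since the 14.64% used for planning is adjusted for confounders; the protocol does not say. What stands is that 0.1 is unlikely and unsupported by anything else in the protocol.
- *The analysis wording need not be a contradiction.* Basing the analysis on individuals can mean pig-level data, and a hierarchical logistic regression is a pig-level analysis. A reader might infer that the trial's type I error is inflated. That holds only if an unadjusted test is meant, and the only model named allows for clustering. The wording still needs reconciling, because it is used to justify omitting the design effect.
- *Stratification.* Randomising within groups of similar baseline prevalence, and adjusting for confounders, should reduce the relevant CV to a within-group one. The power figures above are unstratified and may overstate the loss by an unknown amount. But the sample size calculation claims no such gain.
- *The village numbers are assumed.* This is true, since the protocol fixes none. If the CV is 0.1 and there are 20 or more villages per group, the loss is only a few points.

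**Conclusion.** The point holds as a defect in the power statement. The 80% comes from a formula for independent pigs in a village-randomised trial, and the one figure offered to excuse this sits badly with the range that the protocol reports. The hierarchical model has less than the stated power: about 76%, 65% and 41% at CV 0.1, 0.25 and 0.5 for an assumed 21 villages of 43 per group, unstratified, and less with fewer villages.

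The size of the shortfall is uncertain. It depends on the CV, the number of villages and the gain from stratification, none of which can be settled from the protocol. A reader might take 0.55 as the established CV; it is a rough estimate from two extremes, so the range 0.1 to 0.5 is the fair way to present the result.

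**What to change.** - In Sample size calculation, delete the sentence that dismisses clustering.
- Name one primary analysis: the hierarchical logistic model with village and household effects, with the baseline-prevalence groups used for allocation as strata.
- Recompute the between-village CV, ideally within strata, from the counts of the earlier 21-village survey with binomial noise removed.
- Restate power with a cluster formula suited to the stratified design, for the actual number of villages and over CV 0.1 to 0.5.
- Label 878 as pigs per group, not villages.

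The cost is some protocol wording and one recalculation. Correcting the statement needs no extra pigs, but the stated power becomes less favourable. If 80% is to remain the aim, the recalculation will show whether the available villages can provide it.

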##### Study area

Mbulu District is located in north-eastern Tanzania, between latitude 3.80o-4.50oS and longitude 35.00o-36.00oE. The altitude varies from 1000-2400 m above sea level. The area has a semi-arid and sub-humid climate and receives an annual rainfall of less than 400 mm and over 1200 mm respectively. The long rainy season extends from about March to Mid-May and the short rainy period extends from November to December. Relative humidity ranges from 55%-75% and mean annual temperature ranges from 15oC-24oC. The District has 59 villages and the 1997 District census showed that it had a population of 200 000 people and 32 883 pigs. Crop and livestock production is by far the most important economic activity, employing over 90% of the total District labour force. Most of the inhabitants are Iraqw tribe that occupies most of the highland areas and practices mixed farming. Pigs are raised in most households as a source of income and animal protein for the household. Most of the pigs are let free to graze particularly after harvesting. When there are crops in the fields most pigs are tethered at the backyard and are fed on cut grass, kitchen leftovers, pumpkins and maize grains. Few farmers house their pigs. Slaughtering of pigs takes place at home although few of the pigs are slaughtered at a nearby open slaughter slab. Some home slaughtered pigs are inspected by a meat inspector while some are not. Besides pig farming, villagers also raise other livestock including cattle, sheep, goats, and chicken. Some villagers keep dogs, cats, as well as donkeys.

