##### Data collection methods and experimental procedure

##### Pre-intervention examination of the study population:

A structured questionnaire will be used to collect demographic data of all the study participants. In-depth interviews of five farmers in each village will be done to study human perceptions of the disease. Structured observations will be done in all selected households to study practices related to the transmission of the disease such as pig rearing practices, use and status of latrine, boiling of water for drinking, washing hands before eating and after using a latrine, and eating of infected pig meat.

All pigs in the household will be examined by the researcher using lingual palpation and blood samples collected for antigen ELISA.

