# Post-intervention examination of the study population:

The researcher will reassess perceptions and practices immediately after the intervention and at the end of the study. All pigs born after the intervention will be examined. Similar methods of data collection used in the pre-intervention study will be used in this study. However, the last questionnaire interview will include a question designed to investigate if the participants in the control group have received any information regarding the health education from the intervention group in order to take care for possible confounder during data analysis. The research will also investigate if there has been any change in hygiene policy at any time during the study.

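### The trial is sized in pigs with every pig farmer enrolled and no minimum number of villages, so the stated 80% power is not delivered for a village-randomised comparison

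*Protocol*

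**What the plan says.** Under Phase three, "The village will be the unit of intervention allocation". Under Study population, the sample size is calculated for individual pigs because "there was little variation in the prevalence of porcine cysticercosis in different villages (coefficient of variation was about 0.1". The sentence before the calculation calls the result a number of villages, but the formula defines n as pigs, and the conclusion is that "Approximately 900 pigs will be examined in each of the two groups", once before and once after the intervention.

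The selection rule follows: "The number of villages to be included in the study will depend on the number of pig farmers available in the villages", and "All pig farmers in the selected villages will be enrolled in the study". The pilot study is to collect an updated census of pig farmers to help settle the number of villages. At baseline, "All pigs in the household will be examined by the researcher using lingual palpation". At follow-up, "All pigs born after the intervention will be examined". No minimum number of villages per group appears anywhere.

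The size of a village can be gauged from the Study area section: "The District has 59 villages and the 1997 District census showed that it had a population of 200 000 people and 32 883 pigs". The Statistical analysis section plans a hierarchical logistic model that recognises clustering in households and villages.

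**The concern.** In a village-randomised trial, the strength of the comparison depends first on how many villages are allocated and only then on how many pigs are examined in each. Here the order is reversed. The pig total is fixed, whole villages are taken, and the number of randomised units is whatever remains. The larger the villages, the fewer there will be.

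At stake is the main outcome. A handful of villages per group leaves few degrees of freedom, a poor estimate of between-village variation for the planned hierarchical model, and power well under the stated 80%. The number of villages cannot be repaired after allocation.

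**Working it through.** **Inputs.** From Study population: control prevalence 14.64%, intervention prevalence 10.23%, z values 1.96 and 0.84, about 900 pigs per group, CV about 0.1. From Study area: 59 villages, 32 883 pigs. From the Introduction: earlier survey of 770 pigs in 21 villages, 425 households observed, prevalence 17.4%, village range 3.2-46.7%. From Study limitations: 1.8 pigs per farmer.

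**1. The plan's own figure.** n = (1.96 + 0.84)² × 2 × 0.1244 × (1 − 0.1244) / (0.1464 − 0.1023)² = 878.20. It reproduces. With 900 independent pigs per group the power is 81%. No term involves villages.

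**2. Villages implied.** 32 883 / 59 = 557 pigs per village; 900 / 557 = 1.6 villages, so about two per group. If only a share of the census count is examinable (assumed): 50% gives 900 / 279 = 3.2 villages, 25% gives 900 / 139 = 6.5.

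**3. Power at village level.** Let c be villages per group, m = 900 / c pigs per village, k the CV, p1 = 0.1464 and p2 = 0.1023.

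SE² = {[p1(1 − p1) + p2(1 − p2)] / m + k²(p1² + p2²)} / c = {0.2168 / m + 0.0319 k²} / c, with a two-sided 5% t-test on 2c − 2 degrees of freedom (noncentral t).

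For c = 2, m = 450, k = 0.1: (0.000482 + 0.000319) / 2 = 0.000400, so SE = 0.0200. The ratio is 0.0441 / 0.0200 = 2.20 against a critical t of 4.30 on 2 degrees of freedom, and power is 25%.

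| Villages per group | Pigs per village | Power, CV 0.1 (protocol) | Power, CV 0.25 (assumed) | Power, CV 0.5 (assumed) |
|---|---|---|---|---|
| 2 | 450 | 25% | 12% | 7% |
| 3 | 300 | 44% | 21% | 10% |
| 4 | 225 | 54% | 28% | 12% |
| 6 | 150 | 64% | 38% | 17% |
| 7 | 129 | 67% | 42% | 19% |
| 15 | 60 | 75% | 60% | 33% |
| 21 | 43 | 77% | 65% | 41% |
| 29 | 31 | 78% | 69% | 48% |

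Twenty-nine per group is the largest equal split of 59 villages.

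**4. Permutation limit with two villages per group.** Unstratified, there are 6 allocations and the smallest two-sided p is 2/6 = 0.33. Randomised in two pairs, there are 4 allocations and it is 2/4 = 0.5.

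**5. Is a CV of 0.1 plausible?** The village range is 43.5 percentage points. For 21 roughly normal values the expected range is about 3.78 standard deviations, so the SD is about 43.5 / 3.78 = 11.5 points and the raw CV 11.5 / 17.4 = 0.66. With 770 / 21 = 37 pigs per village, sampling error alone gives √(0.174 × 0.826 / 37) / 0.174 = 0.36. Removing it leaves √(0.66² − 0.36²), about 0.55. This is rough, since it assumes equal village samples and normality, but it lies far from 0.1.

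**The case against.** **Two villages per group is nowhere planned.** This is the strongest reply, and it stands. The protocol has no rule to recruit until 900 pigs are reached. It waits for an updated pig-farmer census from the pilot, and 557 is a 1997 district average. Follow-up is of pigs born after the intervention, Study limitations doubts there will be enough of them, and swine fever may reduce the herd. All this pushes the count above two. The text also mentions selected households under the pre-intervention examination, which sits uneasily with enrolling every farmer. None of it sets a floor, however, and at 3 to 7 villages per group power at CV 0.1 is still only 44-67%.

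**The earlier survey had about 37 pigs per village, which would give about 25 villages per group.** That survey observed about 425 / 21 = 20 households per village, against roughly 557 / 1.8 = 310 pig farmers on the census. It looks like a sample within villages, which the present rule does not provide for.

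**With a CV of 0.1, clustering can be ignored.** The 25% already uses 0.1. Ignoring the degrees-of-freedom penalty, a normal approximation gives about 60% with two villages per group. Grouping villages by baseline prevalence could lower the effective CV, but even at zero the same t-test gives 36% with two per group and 74% with seven.

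**Stronger readings to avoid.** A reader might infer that village and intervention effects cannot be separated at all. That describes one village per group. With two, power at CV 0.1 rises to about 48% as pigs per village become unlimited (SE² = 0.000319 / 2). A reader might also take four allocations and p = 0.5 as the design, but the protocol never says how many prevalence groups there will be.

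**Conclusion.** The point holds in conditional form. The protocol fixes pigs, takes whole villages and leaves the number of randomised units without a floor. Its own figures imply about two villages per group, or about 3 to 7 under the assumed shares of 50% and 25%. At its own CV of 0.1, power is about 25% with two, 44-67% with 3 to 7, and still 78% at the largest equal split of the district. The 80% claim therefore fails at 900 pigs per group whatever the village count.

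The figures rest on a village-level t-test with equal village sizes, as a stand-in for the planned hierarchical model, and on 900 pigs actually being examined per group. The CVs of 0.25 and 0.5 are assumptions; the earlier survey's village range suggests that 0.1 is optimistic. The documents do not support calling this a two-village-per-group trial, nor saying that more villages alone would restore 80%.

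**What to change.** In the Study population section, once the pilot census is available:

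- Set a minimum number of villages per group before fixing the pigs per village.
- Replace enrolment of all pig farmers with a random sample of pig-keeping households in each village, so that about the same 900 pigs per group are spread over as many villages as the geographical separation in Study limitations allows. Base the household number on the expected yield of pigs born after the intervention, not only on 1.8 pigs per farmer.
- Put a justified between-village CV into the sample size formula, reconciled with the 3.2-46.7% range, and restate the power for the chosen number of villages. At 900 pigs per group it will be below 80%. Reaching 80% would need more pigs as well: at CV 0.1, four villages per group with 557 pigs each (2 228 per group) give about 79%, and five (2 785) about 90%.

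The cost of spreading the sample is more villages to visit, more educators to train, more sessions for the researcher to attend, fewer buffer villages and so more risk of information leaking to controls, and a less favourable stated power. As an illustration, 15-21 villages per group would take 30-42 of the 59, which strains that separation, so the number has to be a compromise and be stated as one.
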